### Interim analyses {21b}

No interim analysis is planned in the study.

### Methods for additional analyses (e.g., subgroup analyses) {20b}

The analysis of LSaO_2_, the volume of the UA, and the total score of OSA-20 in secondary endpoints will use similar statistical methods as those used for the AHI. Descriptive statistical analysis will be used for the measurements of lateral cephalometric film and UA.

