Therefore, clinical workers wondered whether it was necessary for all children with OSAHS to go to an orthodontist. Rapid maxillary expansion (RME) and mandibular advancement devices (MADs) are the most commonly used appliances for children with OSAHS [37–41]. RME benefits children with OSAHS through the following mechanisms: (1) it enlarges the dimension of the nasal cavity and increases nasal respiration; (2) it increases the maxillary width so that a better tongue position can be induced; (3) the normal width of the dental arch stimulates the development of the lower jaw. Camacho et al. stated in a systematic review that RME has stable long-term efficacy for pediatric OSAHS patients with transverse maxillary deficiency or narrow hard palates [39]. Villa et al. assessed the outcome of AT and RME in a non-randomized controlled trial and found that both of these treatment methods were effective, but further studies were needed to evaluate their long-term efficacy [42].

MADs, in the form of oral appliances, can promote the anterior displacement of the mandible and hyoid bone, leading to anterior traction of the tongue and thus an enlarged UA dimension. Pavoni et al. found that after MAD treatment, significant improvements in sagittal airway dimensions, hyoid position, and tongue position were induced, and obvious relief in subjective symptoms was observed in children with sleep-disordered breathing [43]. Many studies have reported that the clinical use of functional therapy for mandibular advancement such as twin-block and Frankel appliances significantly reduced AHI in patients with OSAHS [10, 40, 41]. In recent years, the combination of RME and MADs was illustrated by some clinicians.

For OSAHS children with adenotonsillar hypertrophy and dentoskeletal Class II malocclusions, who represent a large proportion of pediatric OSAHS patients, both orthodontic treatment and AT may be effective, but little evidence-based medical research has been found to our knowledge. There have been longstanding debates among clinicians about the indications for AT, especially for children with mild OSAHS. More convincing evidence is needed to prove that AT/orthodontic treatment has a therapeutic effect for children with OSAHS and that it improves the craniomaxillofacial deformity caused by mouth breathing.

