### Objectives {7}

This clinical trial was designed to investigate the efficacy of AT and/or orthodontic treatment for OSAHS children with mild mandibular retrognathia. The efficacy will be evaluated by the improvement in subjective symptoms, polysomnography (PSG) data, UA structure, and maxillofacial development.

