## Interventions

### Explanation for the choice of comparators {6b}

Due to poor compliance, the application of CPAP for pediatric OSAHS is decreasing in the clinic. The most commonly used treatments are medication, AT, and orthodontic treatment. For children with mild OSAHS and mandibular retrognathia, both orthodontic treatment and AT may be effective in terms of PSG data and maxillofacial development, but there is no evidence-based medical research to compare the efficacy of AT and/or orthodontic treatment. Furthermore, we wondered what the indications are for the use of these two therapies, individually or in combination. Thus, in this study, the comparators included a drug treatment group, a surgical treatment group, an orthodontic treatment group, and a surgery and postoperative orthodontic group.

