#### Secondary endpoints

The secondary endpoints will consist of the lowest oxyhemoglobin saturation (LSaO_2_), apnea index, and hypopnea index assessed by PSG, subjective symptoms (assessed by the OSA-20 questionnaire), cephalometric measurements, and morphologic analysis of the UA.

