#### Cephalometric measurements

Lateral cephalometric radiographs will be taken for all the subjects at the intercuspal occlusion and then traced and digitized using the software Dolphin Imaging (Dolphin Imaging & Management Solutions Corporation, Chatsworth, CA, USA). The cephalometric measurements are presented in Fig. 3. The measurement items are as follows: SNA, angular indicator for assessment of maxillary protrusion; SNB, angular indicator for assessment of mandibular protrusion; ANB, angular indicator for assessment of the sagittal relationship between the jaws; MP-FH, angle between the mandibular plane and Frankfort plane; MP-SN, angle between the mandibular plane and SN plane; UI-SN, angular indicator for assessment of upper anterior teeth protrusion; LI-MP, angular indicator for assessment of lower anterior teeth protrusion; UL-Ep, distance between upper lip and the aesthetic plane; LL-Ep, distance between lower lip and the aesthetic plane.

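### Maxillofacial development is one of four stated efficacy domains, but it is the only one with no planned inferential comparison between arms

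*Protocol article*

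**What the plan says.** The Objectives {7} section of the protocol article sets out how efficacy will be judged: "The efficacy will be evaluated by the improvement in subjective symptoms, polysomnography (PSG) data, UA structure, and maxillofacial development". The section on the choice of comparators {6b} names the same domain when it explains why these treatments are compared: for these children, "both orthodontic treatment and AT may be effective in terms of PSG data and maxillofacial development". It adds that comparative evidence is lacking.

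Cephalometry is a secondary endpoint, in a list that includes "subjective symptoms (assessed by the OSA-20 questionnaire), cephalometric measurements, and morphologic analysis of the UA". The Cephalometric measurements section lists nine items, among them "SNB, angular indicator for assessment of mandibular protrusion; ANB, angular indicator for assessment of the sagittal relationship between the jaws". Table 1 schedules lateral cephalometry at M 0, M 7, M 12 and M 24.

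The statistical methods section {20a} specifies ANCOVA for change in AHI from M 0 to M 7, adjusted for gender, obesity status and baseline AHI. The additional analyses section {20b} extends that approach to three secondary measures. LSaO2 is one of them, and the other two appear in this wording: "the volume of the UA, and the total score of OSA-20 in secondary endpoints will use similar statistical methods as those used for the AHI". The next sentence reads: "Descriptive statistical analysis will be used for the measurements of lateral cephalometric film and UA".

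**The concern.** The plan sorts its secondary measures into those that get the AHI method and those that are described. Cephalometry falls in the second group, although it is the only route by which the trial measures an efficacy domain named in its own objective.

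The children are 7 to 10 years old at entry and are followed to 24 months. Jaw angles may change with growth alone over that time, so a mean change within an arm does not separate treatment from growth. A randomised contrast between arms does, but the reader needs an estimate of the difference and its uncertainty to use it.

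There is also a risk of later selection. If between-arm comparisons are added once data are seen, nine items, three follow-up visits and six pairs of arms offer 9 × 3 × 6 = 162 candidate contrasts. Naming one measure and one visit now closes that off.

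**Working it through.** **Step 1. Match each efficacy domain to its planned between-arm analysis.**

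| Domain in Objectives {7} | Measure | Method in {20a} or {20b} |
|---|---|---|
| PSG data | AHI; LSaO2 | ANCOVA; similar method |
| Subjective symptoms | OSA-20 total | similar method |
| UA structure | UA volume | similar method |
| Maxillofacial development | nine cephalometric items | descriptive |

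Three domains keep at least one inferential comparison and the fourth keeps none. The ANCOVA in {20a} cannot be read as covering cephalometry by default, because it is tied to change in AHI and adjusts for baseline AHI. No other section assigns a test or model to the cephalometric items.

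**Step 2. Is this a detail left to an analysis plan?** No. Section {20a} already promises descriptive analysis of all variables. The sentence in {20b} therefore adds something only if it means description in place of the AHI method. It is a stated choice.

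**Step 3. Would the sample size support a comparison?** The protocol gives no precision or power figure for cephalometry, so there is none to reproduce. Its sample size concerns AHI only: 80 per group × 4 = 320, and 320 × 1.10 = 352, the stated total. The derivation of the 80 is a separate matter on which this point does not depend.

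Inputs: n = 80 evaluable per arm (Sample size {14}), two-sided alpha 0.05 (the level is stated; two-sided is my assumption), power 80%. SD is the standard deviation of the change after covariate adjustment, which the protocol does not give, so results are in SD units.

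- 95% CI half-width for one pairwise difference: 1.96 × SD × √(2/80) = 1.96 × 0.158 × SD = 0.31 SD.
- Detectable difference at 80% power, one pair, unadjusted: (1.96 + 0.84) × 0.158 × SD = 0.44 SD by the normal approximation; the t-based calculation gives 0.446, so about 0.45 SD.
- Four arms give 4 × 3 / 2 = 6 pairs. With Bonferroni at 0.05/6, the t-based detectable difference is about 0.56 SD.

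Taking 352 less 10% gives about 79 per arm, and the half-width is still 0.31 SD.

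**Step 4. Illustration in degrees.** Purely as an assumption, let the SD of ANB change be 1 to 2 degrees.

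| Quantity | SD 1° | SD 2° |
|---|---|---|
| CI half-width | 0.31° | 0.62° |
| Detectable, unadjusted | 0.45° | 0.89° |
| Detectable, Bonferroni over six | 0.56° | 1.11° |

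The planned size alone does not rule out a useful between-arm estimate.

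**The case against.** Describing a secondary endpoint is legitimate. With nine cephalometric items and four arms, reserving inference for AHI, LSaO2, UA volume and OSA-20 total is a sensible way to limit multiplicity, and the Trial design section calls the study a pilot. The objective speaks of improvement and does not promise a formal test in every domain. The Background statement that evidence is needed that treatment works and that "it improves the craniomaxillofacial deformity caused by mouth breathing" describes what the field lacks; it is not a trial objective. All of this stands, and it shows that the descriptive choice is not an error in itself. What remains is the mismatch with the Objectives and with the reason given for the comparators. Limiting multiplicity explains describing eight of the nine items; it does not require describing all of them.

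A reader might infer three stronger things that the documents do not support:

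- **That the trial makes no comparison between arms on the jaws.** Summaries by randomised arm can be set side by side; what is missing is a planned estimate with CI, or a test.
- **That {20b} contradicts itself by putting UA volume under the AHI method and UA measurements under description.** Fig. 4 shows other UA measures, such as the minimum cross-sectional area. The natural reading is that volume is tested and the rest described, so this is a wording clarification and not a separate defect.
- **That ANB is the entry criterion for the trial.** The inclusion criteria accept a constricted dental arch or mandibular retraction, and the ANB threshold belongs to the second alternative.

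**Conclusion.** The point holds in a limited form. As written, maxillofacial development is the only one of four efficacy domains without a planned inferential between-arm comparison, although the protocol gives the lack of comparative evidence on it as a reason for the comparators. The primary endpoint, its analysis and the sample size are not affected. It is a cheap improvement and not a threat to the trial's main result.

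The conclusion rests on the text alone. The feasibility figures in SD units assume 80 evaluable children per arm and two-sided testing. The figures in degrees rest on an assumed SD and are only illustrative.

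**What to change.** In {20b}, name one key cephalometric measure and one visit. Change in ANB is a reasonable candidate: it is the only cephalometric value with an entry threshold, though in one of two alternative entry conditions. The visit could be M 7, to match the AHI analysis, or a later one fixed in advance. Analyse it by ANCOVA adjusted for gender, obesity status and the baseline value of the same measure. Report between-arm differences with 95% CI, labelled secondary, and say whether the pairwise contrasts are adjusted for multiplicity. Keep the other cephalometric items descriptive. In the same edit, add a clause saying that UA volume gets the AHI method and other UA measures are described.

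The cost is one secondary model on data already scheduled, with up to six more pairwise contrasts. If the investigators prefer description only, the alternative is to narrow the Objectives and the comparator rationale so that they do not present maxillofacial development as a domain on which the arms will be compared. That costs only wording, but leaves that question without a planned answer.

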### Methods in analysis to handle protocol non-adherence and any statistical methods to handle missing data {20c}

Missing data will be dealt with using the last-observation-carried-forward (LOCF) method.

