### Outcomes {12}

Endpoint measurements will be performed before the treatment (baseline survey; month 0) and at 7 months (M 7), 12 months (M 12), and 24 months (M 24) after the starting point.

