#### Primary endpoint

The primary endpoint of the trial is the mean change in AHI from baseline (M 0) to the primary endpoint (M 7), because PSG is still the gold criterion for diagnosing OSAHS. All subjects will undergo attended overnight PSG in a hospitalized ward. They will go to bed at their usual sleeping time and sleep for at least 6 h to ensure PSG monitoring time. A reduction in airflow of more than 90% compared to that preceding sleep breathing is considered to be an obstructive apnea. A hypopnea is defined as a reduction in airflow of more than 30%, accompanied with an oxygen desaturation of ≥ 3% and/or an arousal. A duration of the obstructive apnea or hypopnea equal to or greater than two respiratory cycles is defined as an obstructive event. The definition of AHI is the number of obstructive events per hour. The analysis will include mixed events but not central events.

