## Statistical methods

### Statistical methods for primary and secondary outcomes {20a}

Statistical analysis will be conducted using IBM SPSS Statistics (version 22.0). Descriptive analysis will be performed for all of our variates. The analysis set will consist of the intention-to-treat (ITT) set, per protocol (PP) set, and safety set. All subjects will be included in the ITT set after randomization regardless of whether they received the treatment or not. Subjects who complete treatment sessions (M 0 to M 7) without any major violation to the trial procedure will be included in the PP set. Participants who receive treatment will be included in the safety set for safety analysis. The significance level will be set so that *P* < 0.05 will be considered significant.

The primary endpoint of this study is the change in AHI from M 0 to M 7. Intergroup comparisons will be performed using an analysis of covariance (ANCOVA) to adjust for gender, obesity status, and baseline AHI. The outcomes will be mainly analyzed using the PP set. Linear regression will be used to evaluate the correlation between observed differences of AHI and the potential prognostic factors, such as gender, BMI, neck size, and research site.

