This study protocol still faces several limitations and challenges. The first is the challenge of sample selection of children with mild OSAHS and mandibular retrognathia. Due to the limited acceptance of randomization, it may take a long time to collect the sample size required for this study. The second is the challenge of subjects’ compliance. Additional services will be provided for participants through WeChat or phone to arrange treatment times and enhance adherence. The third limitation is the consistency of treatment. Before the study begins, all of the surgical and orthodontic treatment teams will receive specific training on the normalized research procedure to ensure consistency.

The results of this study will provide valuable evidence for the merits and long-term efficacy of different treatment approaches and contribute to facilitating the multidisciplinary treatment of pediatric OSAHS.

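### LOCF sets every missing month-7 AHI change in the ITT analysis to zero and freezes later values, so the ITT result is not a sound check on the per-protocol result

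*Protocol article*

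**What the plan says.** The protocol article's section on non-adherence and missing data {20c} contains a single rule: "Missing data will be dealt with using the last-observation-carried-forward (LOCF) method". It does not limit the rule to post-baseline values, and it names no alternative and no sensitivity analysis.

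Under Outcomes {12}, endpoints are measured "before the treatment (baseline survey; month 0) and at 7 months (M 7), 12 months (M 12), and 24 months (M 24"). Table 1 shows the polysomnogram at the same four times. Statistical methods {20a} states: "The primary endpoint of this study is the change in AHI from M 0 to M 7". The planned model is given there too: "Intergroup comparisons will be performed using an analysis of covariance (ANCOVA) to adjust for gender, obesity status, and baseline AHI".

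Two efficacy sets are defined in {20a}. For ITT: "All subjects will be included in the ITT set after randomization regardless of whether they received the treatment or not". For per-protocol (PP): "Subjects who complete treatment sessions (M 0 to M 7) without any major violation to the trial procedure will be included in the PP set". The section names PP as the main set for the outcomes. The section on additional analyses {20b} extends similar methods to LSaO2, upper-airway volume and the OSA-20 total.

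On the longer term, the Discussion says: "The results of this study will provide valuable evidence for the merits and long-term efficacy of different treatment approaches".

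**The concern.** Between baseline and the month-7 endpoint there is no other AHI measurement. Carrying the last observation forward therefore means carrying baseline, and the imputed change is zero by construction. Zero is not a neutral value here. Every treatment or comparison group that the sample size section cites had a non-zero mean change, and children are enrolled on an abnormal sleep study, so some regression to the mean is expected even without an effective treatment. The imputed zeros are then analysed as if they had been observed.

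At stake is the one analysis that keeps every child as randomised. PP compares selected completers, so ITT is the natural check on it. If the ITT estimate depends on how many children each arm lost, agreement or disagreement between the two sets says little. At months 12 and 24 the rule supplies an assumed course for exactly the children whose later course is unknown, in a trial that offers evidence on long-term efficacy.

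**Working it through.** **Inputs from the protocol.** Sample size {14}: 80 per group, about 10% dropout, 352 in total; an effect value of 0.4 tied to an AHI difference of 2.9; cited mean AHI changes of −0.8 (adenotonsillectomy in mild disease), +2.1 (watchful waiting), −2.0 (drug) and −3.7 (orthodontic). Allocation is 1:1:1:1.

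**Plan's own figure.** 4 × 80 = 320; 320 × 1.10 = 352; 352 / 4 = 88 randomised per arm. This reproduces, and 88 per arm is used below.

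**Assumptions, not in the protocol.** Loss by arm; SDs of 2, 2.5 and 4; missing children would have had the same mean change as the others in their arm. The protocol states no SD. If 0.4 is a standardised difference, the implied SD is 2.9 / 0.4 = 7.25.

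**Step 1: mean under zero imputation.** With share p missing and true mean change μ, the arm's expected mean is (1 − p)μ.

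**Step 2: equal loss.** The contrast becomes (1 − p)(μ₁ − μ₂). At p = 0.10:
- drug versus orthodontic: 1.70 × 0.90 = 1.53
- adenotonsillectomy versus watchful waiting: 2.90 × 0.90 = 2.61
- 0.40 SD × 0.90 = 0.36 SD

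With no true difference the contrast stays at 0, so type I error is not raised.

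**Step 3: unequal loss with a true difference.** Drug versus orthodontic, true difference 1.70:
- drug 5%, orthodontic 15%: 0.85 × 3.7 − 0.95 × 2.0 = 3.145 − 1.900 = 1.245
- drug 15%, orthodontic 5%: 0.95 × 3.7 − 0.85 × 2.0 = 3.515 − 1.700 = 1.815
- drug 20%, orthodontic 0%: 3.7 − 0.80 × 2.0 = 2.10

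The contrast can shrink or grow.

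**Step 4: unequal loss with no true difference.** The false difference is |μ|(p₂ − p₁). The variance in each arm is (1 − p)(SD² + μ²) − [(1 − p)μ]². The standard error is √[(v₁ + v₂)/88], and the two-sided error rate at a nominal 5% follows from a normal approximation to the unadjusted comparison.

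Worked case, μ = −2.0, SD 2, 5% versus 15%: v₁ = 0.95 × 8 − 1.9² = 3.99; v₂ = 0.85 × 8 − 1.7² = 3.91; SE = √(7.90/88) = 0.300; 0.20/0.300 = 0.67; error rate 10.2%.

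| True change, both arms | Loss | False difference (events/h) | SD 2 | SD 2.5 | SD 4 | SD 7.25 |
|---|---|---|---|---|---|---|
| −2.0 | 5% vs 15% | 0.20 | 10.2% | 8.4% | 6.4% | 5.4% |
| −2.0 | 5% vs 25% | 0.40 | 27.1% | 19.7% | 10.9% | 6.8% |
| −0.8 | 5% vs 15% | 0.08 | 5.9% | 5.6% | 5.2% | 5.1% |
| −0.8 | 5% vs 25% | 0.16 | 8.8% | 7.4% | 6.0% | 5.3% |

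Simulating the same cases agrees to within half a percentage point. The planned ANCOVA does not remove the false difference: baseline is balanced in expectation by randomisation, and the excess zeros belong to the arm.

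**Step 5: months 12 and 24.** The value carried depends on what the child has.
- Last seen at month 12: month 12 is carried to month 24.
- Last seen at month 7: month 7 is carried to months 12 and 24.
- Never seen after baseline: baseline is carried throughout, so the change is 0.

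The first two cases assume that nothing changes after the last visit; the third assumes no response. A child who misses month 7 but returns at month 12 still gets a zero at month 7, although a later measurement exists.

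**The case against.** The strongest reply is that PP is the main set. It is limited to children who complete months 0 to 7 without major violation, so most children who would receive an imputed zero are outside the headline month-7 analysis. That stands. A reader might infer that LOCF corrupts the main primary result; the protocol does not support this. Two exposures remain. The PP definition turns on completing treatment sessions and does not exclude a child who did so but missed the month-7 sleep study. PP status is also settled at month 7, so PP children lost later are still imputed at months 12 and 24.

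A second reply is that the inflated error rates need assumptions. That stands too. The protocol gives about 10% dropout overall and nothing by arm; a loss of 5% versus 25% averages 15%, above plan. The larger error rates appear only at low SDs and a true change near −2.0. An SD of 7.25 looks large for children selected for mild disease, but it is the only one that can be derived from the protocol. One might infer that losses will differ between spray, surgery and appliance. That is plausible, and the Discussion names compliance as a challenge, but no rate supports it.

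A third inference, that LOCF always assumes durability at months 12 and 24, fails for children never seen after baseline. Nor is LOCF reliably conservative, as Step 3 shows.

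**Conclusion.** The concern holds for the ITT analysis and the later visits. That a missing month-7 AHI becomes a change of exactly 0 follows from the protocol's own schedule, endpoint and ITT definition, and needs no outside assumption. It would fail only if LOCF were restricted to post-baseline values, and the protocol sets no such limit.

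On size, equal loss at the planned 10% costs 10% of every contrast and no type I error. With unequal loss, the false difference is the true change times the gap in loss: 0.20 events/h for 5% versus 15% at −2.0, but only 0.08 at −0.8. The error rate for 5% versus 15% at −2.0 runs from about 10% at SD 2 to about 5% at SD 7.25. These figures assume the loss rates by arm and, apart from 7.25, the SDs. They describe the ITT comparison, not the PP headline. The rule should be replaced before analysis, because it weakens the check on the main result and the long-term evidence.

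**What to change.** In {20c}, replace LOCF with one of two methods for the ITT set:
- multiple imputation by arm ahead of the planned ANCOVA, using baseline AHI, sex, obesity status and any later sleep-study values; or
- a likelihood-based repeated-measures model over all visits with baseline kept as an outcome, taking the month-7 contrast as the endpoint.

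A mixed model fitted only to change scores would not be enough: a child with no post-baseline sleep study contributes no outcome record to it.

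Add a delta-adjusted sensitivity analysis for children with no post-baseline study. State whether a child who completed treatment but missed the month-7 study belongs to PP. Apply the same handling to LSaO2, upper-airway volume and OSA-20.

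The cost is analysis-plan wording and modest programming, reliance on a missing-at-random assumption in the main imputation (which the delta adjustment probes), and slightly wider intervals. No new data are needed.
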